#### Motivation and Notification Levels

Before the trial begins, we will ask participants to self-report their motivation level to learn their results on a 5-point ordinal scale (see Multimedia Appendix 2). Also, participants will be randomized into two notification levels (light or moderate). However, since Apple does not allow iOS apps submitted to the App Store to require that users allow app notifications, we will also record the number of participants that turn off notifications. We anticipate that the number of individuals that turn off notifications will be rare, in part due to a warning message we included as a modal in the app that discourages this behavior, due to the likelihood of failure to complete study tasks according to the user-specified daily schedule (see Multimedia Appendix 1).

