### Power and Sample Size

The study will be sufficiently powered (>80%; alpha=0.05) if 640 individuals begin the study, are randomized into 3 study lengths (5, 15, or 27 days) according to a randomization percent allocation of 20%, 60%, 20%, and achieve rates of completion of 30%, 20%, and 10%, respectively (see Table 3).

**Table 3 table3:** The minimum number of participants we aim to enroll in each study duration.

Study duration	Randomization allocation (%)	Participants who begin study (n)	Estimate of completion rate (%)	Participants who complete study (n)
5-day study	20	128	30	38
15-day study	60	384	20	77
27-day study	20	128	10	13
Total	100	640	60	128

For the sample size estimate, the Hsieh sample size correction for multiple logistic regression was used, which assumes correlation among covariates and therefore adjusts the sample size accordingly [9]. We estimated this correlation to be equal to 0.25. With these assumptions, 97 completed studies are required to discern whether the study length and notification level are associated with the rates of study completion. To estimate how precise we may be, we used sample size tables for each predictor (see Multimedia Appendix 4).

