### Data Analysis Plan

#### Primary Analysis

All study data, unless otherwise noted, will be collected through the N1 app, and stored in Health Insurance Portability and Accountability Act (HIPAA)-compliant cloud storage. Statistical analyses will be conducted primarily using R version 3.6 (The R Foundation, Vienna, Austria). We will use a multiple logistic regression model to discern the relationship between study duration and notification level with the proportion of studies completed among participants who begin a study. Participants who begin a study are defined as those who achieve both treatment adherence and assessment adherence for at least one day during the baseline period. Participants that do not begin the study will be removed from the analysis. We will adjust these results for any variance in completion rate by age and sex.

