We anticipate that most participants will schedule their treatments at the beginning of the day since caffeine consumption is a typical morning ritual. This represents two challenges for participant engagement that may not be generalizable across other N-of-1 trials. First, a recent survey of eight app-based digital health studies observed the highest levels of engagement in the evening [14]. Second, the act of abstaining from caffeine consumption for the duration of the baseline period may be perceived as a significant challenge for some individuals in a manner that may be altogether absent were we to be running a trial that compares two treatments of a different nature.

The estimation of completion rates in the total enrolled population for each study duration is a challenge because it not only depends on factors being evaluated in this study but also on recruitment and user characteristics that are uncontrolled outside of very permissive inclusion/exclusion criteria that focus on the safety of caffeine consumption. The novelty of app-based research, for example, may attract people that are more curious about the app or methods than they are committed to learning their results, which is why we included the question about motivation level as an exploratory measure. For example, one recent app-based research study on asthma experienced very high initial recruitment followed by rapid attrition and a small number of highly engaged participants [17]. The relationship between intrinsic motivation and treatment adherence has been examined elsewhere, such as long-term antiretrovirals for HIV/AIDS, weight loss, and various public health initiatives that involve behavior change [18].

One limitation of the collection of only minimal demographic information is that we will not be able to determine if the enrolled study population is representative of the general population outside of age and sex, which will limit the generalizability of our results. The most extensive study to date on retention in digital health studies showed a relationship between age and retention, with older populations having higher retention than younger participants [14]. They observed no relationship between sex and retention [14].

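### Pre-trial motivation is left out of the primary logistic model; prespecifying it would add a modest amount of power if it is answered before the assignment is known

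*Protocol article*

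**What the plan says.** Under Motivation and Notification Levels the article states: "Before the trial begins, we will ask participants to self-report their motivation level to learn their results on a 5-point ordinal scale". Strengths and Limitations gives the reason: app-based research may draw people who are more curious about the app than committed to their results, "which is why we included the question about motivation level as an exploratory measure".

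Under Primary Analysis, completion among participants who begin is modelled by multiple logistic regression on duration and notification level. The only covariate statement is: "We will adjust these results for any variance in completion rate by age and sex".

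Under Exploratory Analyses, motivation is a covariate in the Bayesian model of daily nonadherence and early withdrawal, which is also adjusted for age and sex.

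Strengths and Limitations also reports that the most extensive earlier study of retention found a relation with age and none with sex.

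**The concern.** Early withdrawal is the complement of the primary outcome. The plan treats motivation as a possible determinant of withdrawal in one model and omits it from the model that tests the two hypotheses. It does adjust for sex, although the evidence it cites found no relation between sex and retention.

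In a randomised comparison, adjusting for a prognostic baseline variable usually raises power. What is at stake is some power for the comparisons with least to spare: notification level, for which the article text gives no effect size, and the contrasts between adjacent durations. Validity is not in question.

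**Working it through.** **Inputs from Power and Sample Size.** 640 participants begin, allocated 20/60/20 (128, 384, 128), and "achieve rates of completion of 30%, 20%, and 10%, respectively". Alpha is 0.05, taken as two-sided because the article does not say. On the correlation among covariates: "We estimated this correlation to be equal to 0.25".

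**Assumptions, not in the documents.** The motivation effect is an odds ratio of 1.25 to 3 per SD. The notification effect is a log odds ratio of 0.5 (odds ratio about 1.65). The distribution of the 5-level score is also assumed.

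**Step 1: the stated power.** The article says: "The study will be sufficiently powered (>80%; alpha=0.05) if 640 individuals begin the study". Overall completion is 0.2×0.30 + 0.6×0.20 + 0.2×0.10 = 0.20. The noncentrality of the 2-df duration test is N Σw(p − p̄)² / [p̄(1 − p̄)] = 640 × 0.004 / 0.16 = 16, which gives 95.7% power. Reading 0.25 as a correlation (640 × 0.9375 = 600) gives 94.4%; reading it as R² (640 × 0.75 = 480) gives 88.3%. The claim of more than 80% is reproduced for duration overall. The 97 required completers do not follow uniquely from the printed inputs, and nothing here depends on that figure.

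**Step 2: where power is thinner.** For two proportions, power = Φ[(|d| − 1.96·SE₀)/SE₁], with SE₀ pooled and SE₁ unpooled.
- 5 vs 15 days: SE₀ = √(0.225×0.775×(1/128 + 1/384)) = 0.0426; SE₁ = √(0.21/128 + 0.16/384) = 0.0454; (0.1 − 0.0835)/0.0454 = 0.363, so power is 64%.
- 15 vs 27 days: 76% by the same formula. 5 vs 27 days: 98%.
- Notification, 320 per arm at 20% overall: 65% at an odds ratio of 1.6 (16.3% vs 23.7%) and 84% at 1.8 (15.4% vs 24.6%).

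**Step 3: adding motivation.** 3,000 simulated trials per setting, n = 640, rates as in Table 3 of the article, logistic model without → with the score. Power in %:

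| Motivation OR per SD | Duration, 2 df | 5 vs 15 days | 27 vs 15 days | Notification |
|---|---|---|---|---|
| 1.25 | 96.4 → 96.5 | 64.1 → 64.3 | 76.3 → 76.5 | 68.9 → 69.0 |
| 1.5 | 96.1 → 96.2 | 62.6 → 63.4 | 76.9 → 77.5 | 68.2 → 69.8 |
| 2 | 96.4 → 97.2 | 64.1 → 66.1 | 75.3 → 77.4 | 65.8 → 68.7 |
| 3 | 96.2 → 98.0 | 63.8 → 69.4 | 76.5 → 80.4 | 59.0 → 63.9 |

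**Step 4: where the gain comes from.** For 5 vs 15 days the standard error of the log odds ratio goes from 0.234 to 0.235, 0.237, 0.243 and 0.253 down the table. It does not fall. The coefficient grows proportionally more: at an odds ratio of 2 it goes from 0.542 to 0.581, so the ratio to its standard error rises from 0.542/0.234 = 2.32 to 0.581/0.243 = 2.39. At an odds ratio of 3 it rises from 0.540/0.234 = 2.31 to 0.626/0.253 = 2.47.

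**Step 5: marginal difference.** The relative fall in its standard error is 1 − √(1 − s), where s is the share of outcome variance explained by motivation, averaged over arms. For a uniform score at an odds ratio of 2, s = 0.2×0.089 + 0.6×0.068 + 0.2×0.038 = 0.066, a fall of 3.4%. Over three assumed score distributions the fall is 0.3–0.4%, 0.9–1.2%, 1.9–3.4% and 3.6–7.4% at odds ratios of 1.25, 1.5, 2 and 3.

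**Second simulation.** With 1,500 trials per setting and a notification odds ratio of about 1.7, notification power goes from 78% to 79%, 76% to 78% and 71% to 77% at log odds ratios of 0.3, 0.6 and 0.9 per level. The direction agrees. The last setting implies an odds ratio of e^3.6, about 37, between the lowest and highest answers.

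**The case against.** The strongest reply is that the plan is consistent. It calls motivation exploratory, models it in the exploratory analysis and leaves it out of the primary one. That stands: the omission is a declared choice and no passages contradict each other. Age, the variable that the cited study did link to retention, is already adjusted for.

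The size of the gain also rests on assumptions. The documents give no figure for the motivation effect, and the larger gains need a strong one. The Monte Carlo standard error of a single power estimate is about 1 point (√(0.65×0.35/3000) = 0.9), so the smallest gains are indistinguishable from none.

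Timing matters too. The article says only that the question comes before the trial begins. It does not say whether that is before the participant learns the assigned duration and notification level, and the participant-flow figure was not available here. If the answer follows disclosure, it may itself be affected by the assignment, and adjusting for it could bias the comparison.

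A reader might infer three stronger things that the documents do not support:
- That precision is being given up at no cost. For a log odds ratio the standard error rises slightly, and adjustment has costs.
- That motivation is expected to drive attrition, or is the strongest predictor collected. The text is tentative and gives no figure.
- That the primary comparison is biased without it. Duration and notification level are randomised. Removing participants who do not begin is a separate question, which a motivation term would not settle.

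**Conclusion.** The point holds as an optional gain in efficiency; the plan contains no error here. The primary model leaves out a pre-trial variable that the protocol itself links to commitment. Across the assumed range no comparison loses power. The gain is negligible for a weak association and worthwhile only for a strong one, and it falls mainly on notification level and the adjacent-duration contrasts; the primary hypothesis, tested overall, has little to gain. These sizes rest on the completion rates in the article's Table 3 and on the assumed motivation and notification effects. The recommendation also depends on the motivation question preceding disclosure of the assignment, which the documents leave open.

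**What to change.** Replace the open-ended covariate sentence under Primary Analysis with a fixed list: age, sex and the motivation score as one linear term, alongside duration and notification level. State that motivation enters only if it is answered before the participant learns the assigned duration and notification level; otherwise keep it in the exploratory model. Report marginal completion differences, averaged over the covariates, beside the odds ratios.

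The cost is one model term and no new data collection. The odds ratios become conditional on motivation, so they are not directly comparable with unadjusted ones. A linear form is assumed for a 5-point ordinal score, and missing answers need a simple rule set in advance.

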#### Exploratory Analyses

We will also use descriptive statistics to summarize measures collected in the Brain Boost Study. We will compare the proportion of studies completed and trial adherence across the six groups of participants (three study durations and two notification levels), removing from this analysis anyone that turned off notifications. We will also compare the proportion of completed trials that are deemed by the N1 app to demonstrate a meaningful difference in treatment response on any of the cognitive tests, across the three study durations.

We also want to learn about the factors that influence the measure of trial adherence to improve future study designs. We will use Bayesian methods for exploratory analysis to get a baseline for future analyses, which we expect will also use Bayesian methods of analysis. The exploratory analysis will utilize a Bayesian survival-style model with semicompeting risks throughout the study. It will be assumed that a participant is in the study up until the time of study completion, voluntary withdrawal, or involuntary withdrawal (ie, study failure). Daily adherence will be assessed among all participants in the study on a given study day. There will be two types of events considered: (1) daily nonadherence, as a nonterminal repeating event; and (2) early withdrawal (including both voluntary withdrawal and involuntary withdrawal due to study failure) as a terminal (nonrepeating) event. The daily rate of nonadherence and early withdrawal will be modeled as a Poisson process with the rates impacted by several covariates, including study day (number of days since the start of the study, estimated with a random walk prior), notification level (light versus moderate); self-reported motivation level (5-point ordinal scale), day of the week (if distinguishable from study day), and subject-specific shared frailty term.

The cumulative probability of early withdrawal can be used to estimate the inverse probability of study completion. Also, the daily rates of adherence can be used to improve study design for future participants, depending on self-reported motivation and subject-specific characteristics. As in the primary analysis of the study completion rate, we will additionally adjust this analysis of adherence for age and sex.

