### Randomization

The study duration is either 5, 15, or 27 days. Participants will be randomized into study duration according to the allocation of 20%, 60%, and 20%, respectively. The uneven allocation to study duration was chosen out of consideration for the trade-offs between various study lengths. While we hypothesize that 5-day study lengths are more likely to be completed, they are also less likely to generate a meaningful result due to the small number of outcome measures. On the other hand, 27-day studies are more likely to generate a meaningful result with more repeated outcome measures, but we hypothesize that they are more likely to result in early withdrawal. Allocating more people to the 15-day study is a reasonable compromise between these two extremes, which is reflected by our decision to allocate more participants into this group while maintaining a sufficient sample size for each group to assess our primary outcome measure, as described below.

Notification level is defined as the frequency participants receive reminders to complete study tasks and is either light or moderate. Participants are randomized into the notification level, such that 50% of participants are in each group. Participants randomized into the light notification group receive two notifications per day: one reminder to take their treatment and one reminder to complete the assessment (see Multimedia Appendix 1). Participants randomized into the moderate notification level receive 4-5 notifications per day: 2 reminders to take their treatments and 2-3 reminders to complete their assessment (see Table 1).

**Table 1 table1:** Notification levels for the Brain Boost Study.

Notification level	Treatment reminders	Assessment reminders
Light	At treatment time	At assessment time
Moderate	15 minutes before At treatment time	15 minutes before At assessment time 15 minutes before the end of assessment window, only if the assessment is incomplete at this time

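### The exploratory six-group comparison drops anyone who turned notifications off, which leaves it open to bias of unknown direction and size

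*Protocol article*

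**What the plan says.** Under Randomization, notification level is a randomised factor: "Participants are randomized into the notification level, such that 50% of participants are in each group". The levels differ in daily load. For light, "Participants randomized into the light notification group receive two notifications per day"; for moderate, "Participants randomized into the moderate notification level receive 4-5 notifications per day".

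Under Motivation and Notification Levels, the protocol explains that the platform owner does not let an app make notifications compulsory, and so "we will also record the number of participants that turn off notifications". It gives no number for how often this will happen: "We anticipate that the number of individuals that turn off notifications will be rare". One reason given is an in-app warning that discourages switching off, "due to the likelihood of failure to complete study tasks according to the user-specified daily schedule".

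Under Exploratory Analyses: "We will compare the proportion of studies completed and trial adherence across the six groups of participants", that is, three durations by two notification levels, and then "removing from this analysis anyone that turned off notifications". No version of this comparison with everyone kept in is stated.

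Two other analyses concern notification level. The primary logistic regression takes participants who begin a study, and the Bayesian model takes all participants still in the study on each day. Neither states an exclusion for notification setting.

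**The concern.** Randomisation makes the groups comparable at the point of assignment. Removing people for something they do afterwards keeps that comparability only if the behaviour is unrelated to the assigned group or unrelated to the outcome. Neither can be assumed here.

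- **Link to assignment.** The two levels differ in how many reminders arrive, and silencing the app is a plausible reaction to that number. A 27-day study also leaves more time to switch off than a 5-day study.
- **Link to outcome.** The protocol makes this link itself: its warning ties switching off to missed tasks. The exclusion also carries no time limit. Someone who is already disengaging and then silences the app would be removed along with their non-completion.

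The article's stated purpose is to inform the design of future app-based N-of-1 trials. A designer can choose a notification level but, on the protocol's own account, cannot oblige users to leave notifications on. The useful quantity is the effect of assigning a level, including any switching off that follows. This is also the only stated comparison of trial adherence across the six groups.

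**Working it through.** The plan gives no figure for this exclusion, so there is none to reproduce. The check asks how far the exclusion alone could move the comparison when notification level truly has no effect.

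**Inputs from the Protocol article**
- 640 begin the study (Power and Sample Size) and allocation to level is 50:50, so 640 × 0.5 = 320 per level.
- Table 3 expects 38 + 77 + 13 = 128 completers, and 128/640 = 20%. This is used as the true completion rate in both levels.

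**Assumptions, not in the document**
- *o*, the share who switch off: from 1% light / 3% moderate up to 10% / 30%.
- *q*, the completion rate among those who switch off, taken as equal in the two levels: 0% to 40%.

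**Formula.** Completion among those kept = (0.20 − *o* × *q*) / (1 − *o*). Bias = moderate minus light, since the true difference is zero.

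Example, 5% / 15% with *q* = 0:
- light: 0.20/0.95 = 21.05%
- moderate: 0.20/0.85 = 23.53%
- bias: +2.48 points

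| Off, light | Off, moderate | *q* | Kept, light | Kept, moderate | Bias (points) |
|---|---|---|---|---|---|
| 1% | 3% | 0% | 20.20% | 20.62% | +0.42 |
| 1% | 3% | 40% | 19.80% | 19.38% | −0.42 |
| 2% | 5% | 0% | 20.41% | 21.05% | +0.64 |
| 5% | 15% | 0% | 21.05% | 23.53% | +2.48 |
| 5% | 15% | 10% | 20.53% | 21.76% | +1.24 |
| 5% | 15% | 40% | 18.95% | 16.47% | −2.48 |
| 10% | 30% | 0% | 22.22% | 28.57% | +6.35 |
| 10% | 10% | 0% | 22.22% | 22.22% | 0 |

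**Chance of a spurious significant result**, pooling over durations, two-sided 5% test assumed, so 2.5% nominal in one direction. For 5% / 15% with *q* = 0:
- numbers kept: 320 × 0.95 = 304 and 320 × 0.85 = 272
- pooled rate: (64 + 64)/576 = 0.222
- standard error: √[0.222 × 0.778 × (1/304 + 1/272)] = 0.0347
- expected z: 0.0248/0.0347 = 0.71
- chance of exceeding 1.96: Φ(0.71 − 1.96), about 11%

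The same calculation for 10% / 30% with *q* = 0 gives about 38%.

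**Reading the table.** The bias vanishes when both levels switch off equally often with the same *q*, or when switchers complete at the same 20% as everyone else. It is positive when switchers complete less often than 20% and negative when they complete more often. At off-rates that fit the word rare (the 1% / 3% and 2% / 5% rows) it stays below 1 point.

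**After the fix.** With everyone kept in the assigned level, both levels show 20% under the same null. The bias is 0 and all 320 per level are retained.

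The same mechanism applies to the duration contrast. The document gives nothing from which to size it, and no figure is offered here.

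**The case against.** The strongest reply is that little depends on this sentence. The effect of notification level on completion is answered by the primary logistic regression, which keeps everyone who begins a study. Daily adherence is handled by the Bayesian model, which keeps all participants in the study on a given day and has notification level as a covariate. The exclusion sits in a comparison labelled exploratory, and an as-delivered view beside an all-beginners model is a common complement. This stands in full as a limit on the scope of the point. It does not remove it. Neither model is stated to give the six-group comparison, and neither analyses the trial-adherence proportion. The covariates named for the Bayesian model do not include study duration.

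A second reply concerns timing. The protocol raises the subject as the app being unable to require that users allow notifications. That wording also fits refusal at the permission step, before any difference in reminder load is felt. Refusal of that kind cannot be caused by the assigned level, and removing those people would not bias the comparison of levels. This also stands. The document does not say when a person counts as having turned notifications off, so the fault is exposure to bias and not bias shown.

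A third reply is that switching off is expected to be rare. If so, the bias is indeed small, but so is anything gained by the exclusion. The expectation carries no number, and the Results section says that beta testing collected no completion or adherence data.

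**Conclusion.** The point holds as a weakness confined to the exploratory six-group comparison. That comparison conditions on a behaviour that can follow randomisation, may depend on both randomised factors, and is tied by the protocol to the outcome. It is therefore open to bias of unknown direction and size. On the stated expectation of rarity the bias in completion is under about 1 point. It reaches about 2.5 points at assumed off-rates of 5% and 15% with no completers among switchers, and more only if switching off is commoner and more unequal. These figures rest on assumed off-rates, an assumed completion rate among switchers, and a true null at 20%.

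A reader might infer something stronger: that the comparison is biased and will favour the moderate level. An illustration with 5% completion among switchers can make that look firm:
- Off-rates of 5% / 20%: (0.20 − 0.0025)/0.95 = 20.8% against (0.20 − 0.01)/0.80 = 23.8%, odds ratio 1.19.
- Off-rates of 5% / 30%: 20.8% against (0.20 − 0.015)/0.70 = 26.4%, odds ratio 1.37.

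The document does not support that reading. It fixes neither the timing, the frequency nor the difference between levels. Moderate off-rates of 20% or 30% are far from rare, and the sign reverses if switchers complete more often than others. The primary conclusion is not in question.

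**What to change.** In Exploratory Analyses:

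1. Make the six-group comparison of completion and trial adherence as randomised, including all participants who begin the study whatever their notification setting.
2. Report the proportion who turned notifications off by assigned level and by study duration.
3. Keep the comparison without these participants, if wanted, only as a labelled sensitivity analysis.

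The change takes one or two sentences and no new data, because the number who turn notifications off is already to be recorded. The statistical cost is that the as-randomised result is a slightly diluted estimate of the effect of reminders actually received. If that second effect is of interest, an instrumental-variable analysis with assignment as the instrument could be added, but it is optional and not part of the required change.

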### Measures

#### The Proportion of Studies Completed

The primary outcome of interest is the proportion of studies completed. A study is considered complete if a participant reaches the end of a trial without a study failure (involuntary withdrawal) or voluntary withdrawal. A study failure occurs when there is insufficient data generated during baseline or any treatment period due to missed treatments (self-reported) or incomplete assessments. Participants must complete all assigned treatment and assessment tasks for 1/3 of the days in each period to avoid study failure and involuntary withdrawal, except for the 5-day study where all tasks must be completed each day because there is only one day per period. For the 15-day and 27-day trials, we inevitably expect participants to miss some tasks during these periods, so we wanted to allow for some nonadherence. While the requirement of task completion for 1/3 of the days in each treatment period is somewhat arbitrary, the choice of 1/3 of the days means that, at a minimum, completed 15-day trials will at least have the same amount of data as completed 5-day trials and are also likely to have more. We applied the same criteria to the 27-day trial so that the criteria for study failure are uniform across all three study durations. It is also worth noting that the 3 study lengths are primarily dictated by our randomized, counterbalanced, crossover design that defines N-of-1 trials: NABBA or NBAAB, where N is baseline, A is treatment period A, B is treatment period B, and AB or BA is a block. The minimum N-of-1 trial for a counterbalanced design with two blocks is five days if you have only one day per treatment period and one day of baseline.

We anticipate that a 27-day trial approaches what is likely to be the maximum number of days we could expect people to participate with reasonable adherence for this study, which requires daily tasks. The 15-day trial splits the difference between these two extremes. Put another way, we chose to vary treatment period lengths by one day for the 5-day trial, three days for the 15-day trial, and five days for the 27-day trial. We could have selected a different design, such as treatment periods that are 1, 2 and 3 days long rather than 1, 3 and 5 days long for each group; however, to evaluate the impact of study durations and notification levels on completion rates, we reasoned it would be better to have a more extensive spread across the three groups.

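### The exploratory Bayesian model gives study failure its own random rate, although missed days and assigned duration fix it, and duration is not a named covariate

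*Protocol article*

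**What the plan says.** The protocol article, under Exploratory Analyses, describes a Bayesian survival-style model with semicompeting risks. The first event is listed as "1) daily nonadherence, as a nonterminal repeating event". The second is "early withdrawal (including both voluntary withdrawal and involuntary withdrawal due to study failure) as a terminal (nonrepeating) event". On the rates it says: "The daily rate of nonadherence and early withdrawal will be modeled as a Poisson process with the rates impacted by several covariates, including study day". The remaining named terms are notification level and "self-reported motivation level (5-point ordinal scale), day of the week (if distinguishable from study day), and subject-specific shared frailty term". A later sentence adds: "we will additionally adjust this analysis of adherence for age and sex". Assigned study duration is not named.

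The failure rule is under The Proportion of Studies Completed: "A study failure occurs when there is insufficient data generated during baseline or any treatment period due to missed treatments (self-reported) or incomplete assessments". For the longer studies, "Participants must complete all assigned treatment and assessment tasks for 1/3 of the days in each period to avoid study failure and involuntary withdrawal"; in the 5-day study every task must be done every day. The Adherence section counts a day as adherent when both the treatment and the assessment task are met, which is the same unit that the failure rule counts. The model has a stated use. Its withdrawal probabilities are to feed an estimate of completion, and its daily adherence rates are to improve later designs.

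**The concern.** The terminal event pools two things of different kinds. Voluntary withdrawal is a decision by the participant and can reasonably have its own random rate. Study failure cannot: once the missed days and the assigned duration are known, whether the participant fails is settled. Giving it a further rate models the same information twice and allows combinations that the rule forbids, such as a 5-day participant who misses a day and stays in the study. In that arm the supposedly nonterminal, repeating event ends the study the first time it happens.

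Duration sets the rule and is the trial's main randomized factor. If the withdrawal rate depends on study day but not on duration, arms with different rules share one curve. Completion probabilities by duration, which a designer of a later N-of-1 trial would want from this model, would then be misleading. Pooling also makes it hard to tell whether notifications reduce quitting or reduce missed tasks.

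**Working it through.** **Inputs.** Treatment periods last 1, 3 and 5 days (The Proportion of Studies Completed). Each study has one baseline and four treatment periods (Study Design). The 27-day baseline is inferred as 27 − 4×5 = 7 days. The required share of days is one third per period. Participants who begin have at least one fully adherent baseline day (Primary Analysis).

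**Reproducing Table 2.** Minimum actions = 2 × the sum over periods of (days ÷ 3, rounded up).

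- 5-day: 2 × (5×1) = 10
- 15-day: 2 × (5×1) = 10
- 27-day: 2 × (3 + 4×2) = 22

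These match Table 2 (10, 10, 22), which confirms the rounding up and the 7-day baseline. Failure therefore needs 1 missed day in the 5-day study, 3 of 3 in a 15-day period, 4 of 5 in a 27-day treatment period, and 5 of 7 in the 27-day baseline.

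**Size.** The documents give no daily nonadherence rate. Assume a constant, independent probability q of missing a day, with p = 1 − q, and no voluntary withdrawal. Rule failure among participants who begin is:

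- 5-day: 1 − p⁴
- 15-day: 1 − (1 − q³)⁴
- 27-day: 1 − (1 − q⁵ − 5pq⁴)⁴ × (1 − q⁷ − 7pq⁶ − 21p²q⁵)/(1 − q⁷)

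In the two shorter studies the baseline drops out, because beginning already satisfies its minimum.

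At q = 0.2:

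- 5-day: 1 − 0.4096 = 59.0%
- 15-day: 1 − 0.992⁴ = 3.2%
- 27-day: 1 − 0.99328⁴ × 0.99534 = 3.1%

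At q = 0.5:

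- 5-day: 1 − 0.0625 = 93.8%
- 15-day: 1 − 0.875⁴ = 41.4%
- 27-day: 1 − 0.8125⁴ × 0.7795 = 66.0%

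| Daily nonadherence (assumed) | 5-day | 15-day | 27-day |
|---|---|---|---|
| 10% | 34.4% | 0.4% | 0.2% |
| 20% | 59.0% | 3.2% | 3.1% |
| 30% | 76.0% | 10.4% | 14.3% |
| 50% | 93.8% | 41.4% | 66.0% |

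Without the restriction to participants who begin, the figures are 67.2%, 3.9% and 3.1% at q = 0.2, and 96.9%, 48.7% and 66.3% at q = 0.5.

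**Reading.** Identical daily behaviour gives very different failure probabilities by arm. The order of the 15- and 27-day studies also reverses between 10% and 30% nonadherence. A constant rate ratio for duration would therefore not carry the rule either; the thresholds have to be applied as such.

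**The case against.** The strongest reply is that this is a condensed description of an exploratory model. A reader might infer that duration is excluded, but the covariate list is introduced as partial, so the text does not say that. A reader might also infer that the two events are linked only through the shared frailty; the text names the frailty but does not say that it is the only link. Both readings go too far. What stands is that failure is expressly placed inside a terminal event with a Poisson rate. Adding duration to that rate, or sharing a frailty with it, does not turn it into a threshold that restarts in each period.

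It can also be said that the composite matches the endpoint, since completion means neither failure nor voluntary withdrawal. That is so, and the composite is a sound quantity to report. The difficulty lies in modelling one of its parts as a free event.

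Three further inferences are tempting and not supported:

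- **Day-by-day failure hazards.** These require a date of failure that the documents do not give. Missed treatments can be recorded at the end of the trial, and some early failures would fall on people who never begin.
- **Poisson as an error.** A Poisson process observed as any or none per day is a complementary log-log binary model, so this is a matter of preference.
- **A reciprocal.** The sentence "The cumulative probability of early withdrawal can be used to estimate the inverse probability of study completion" is loose wording for one minus the withdrawal probability. Nothing suggests that a reciprocal would be computed.

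**Conclusion.** The point holds for the exploratory Bayesian model. The stated terminal event conflicts with the stated failure rule, and the named covariates leave out the factor that sets the rule. With the covariates as listed, arms whose rule-failure probabilities are 59%, 3.2% and 3.1% at 20% daily nonadherence would be averaged, and completion probabilities and design advice would mislead by duration. These sizes rest on an assumed constant, independent rate of missed days and on no voluntary withdrawal. Over the 10% to 50% range shown, the gap between the 5-day study and the others stays large. The structural conflict does not depend on the assumed rate.

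A reader might infer that the trial's main result is compromised. It is not: the primary logistic model includes study duration, and the descriptive comparison of six groups also separates the arms.

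**What to change.** State in the Exploratory Analyses section, before the model is fitted, that:

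1. The random events are daily nonadherence and voluntary withdrawal, and assigned duration is a covariate for both.
2. Study failure is an end of follow-up determined by the observed adherence history, not an event with its own rate.
3. Failure and completion probabilities for each arm come from applying that arm's stated rule to posterior-predicted daily adherence, combined with the modelled voluntary withdrawal.

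The cost is modelling and coding only. The section Other Collected Data already lists dates of adherence, nonadherence, early withdrawal and completion. It does not itemise the type of withdrawal, but rule failure can be identified from the adherence dates. The failure rule, the randomization and the primary analysis stay as they are.
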